
#### Secondary outcome—Physical functions

Physical functions, including *mobility, balance, lower limb muscle strength*, and *estimated cardiorespiratory fitness*, will be assessed using tests and self-reported questionnaires validated for the older adult population. These tests will be performed online and at home under remote supervision. First, mobility will be assessed using the 4-meter walk test and the Timed Up and Go (TUG) performed at spontaneous and fast speeds. During the 4-meter walking test, participants' walking speed will be measured in a straight line over 4 meters. During the TUG, participants will get up from a chair, walk 3 meters, turn around, and sit back in the chair while they are timed. Balance and lower limb muscle strength will be measured by a one-leg balance test (i.e., stay on one leg as long as possible with a maximum duration of 60 s) and a Five-Time-Sit-to-Stand test (i.e., five consecutive sit-to-stand movements done as fast as possible without using arms as leverage), respectively. These mobility and functional tests are all commonly used in a clinical setting and have demonstrated their associations with global cognitive functioning and specific cognitive domains such as processing speed and executive functions [46]. In order to prevent any possibility of falls and secure the participants, before the assessment, each participant will be interviewed about his history of musculoskeletal and sensory disorders (e.g., severe low back pains, recent sprain, vestibular disorders). Also, participants will receive by email a description of each test and its set-up, associated with demonstration videos. Then, the testing set-up will be revised with the participant at the beginning of the functional assessment session to ensure that the participant has enough space and measures the walking tracks for both 4-meter and TUG tests with sufficient precision. Finally, during the testing session, the research team member will verify that they always have suitable visual feedback to ensure the testings' security and reliability. All these dispositions converge with the recently published recommendations for the remote assessment of gait and balance [47]. Finally, the Matthews questionnaire will be used to predict participants’ cardiorespiratory fitness (i.e., VO_2max_) based on sex, age, anthropometric data, and self-reported physical activity level [48].

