**Methods:**

One hundred twenty-two healthy older adults (> 50 years old) will be recruited from the community and randomized to one of the two arms for 6 months: (1) home-based physical exercises monitoring alone and (2) combined physical exercises monitoring with home-based cognitive training. The primary outcome is cognition, including general functioning (Montreal Cognitive Assessment (MoCA) score), as well as executive functions, processing speed, and episodic memory (composite *Z*-scores based on validated neuropsychological tests and computerized tasks). The secondary outcome is physical functions, including balance (one-leg stance test), gait and mobility performance (Timed Up and Go, 4-meter walk test), leg muscle strength (5-time sit-to-stand), and estimated cardiorespiratory fitness (Matthews’ questionnaire). Exploratory outcomes include mood, anxiety, and health-related quality of life as assessed by self-reported questionnaires (i.e., Geriatric depression scale-30 items, Perceived stress scale, State-trait anxiety inventory-36 items, Perseverative thinking questionnaire, Connor-Davidson Resilience Scale 10, and 12-item Short Form Survey).

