### Participants

A total of 122 participants aged 50 and older will be enrolled according to the following inclusion criteria:
Have access to a tablet (i.e., iPad or Android) or a computer with an Internet connection,Absence of significant cognitive impairment (i.e., score of 19/23 or higher on the telephone version of Mini-Mental State Examination, MMSE) [29],Absence of non-cardiopulmonary limitation to exercise (e.g., arthritis) or of a severe exercise intolerance,Absence of respiratory disease (e.g., severe asthma, COPD, severe COVID-19 related symptoms) as documented with a medical questionnaire,Absence of cardiovascular disease (e.g., chronic heart failure, somatic aortic stenosis, atrial fibrillation, malignant arrhythmias, any documented atherosclerosis disease) as documented with a medical questionnaire.

No systematic dropout criteria are fixed as dose-response relationships will be explored.

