### Remote setting and procedures, online data management

There is no on-site visit planned in the course of the study. The research team has implemented online tools that allow performing all assessments, exercise monitoring, and cognitive training entirely remotely. The research project will be advertised to active members of physical exercise centers and to community-dwelling adults through online study announcements (e.g., videos, interviews, newsletters). Potential participants will be able to express their interest by leaving a voice mail or sending an email to an email address dedicated to the study. The name and contact information of potential participants will be compiled in a password-protected encrypted file located in a cloud folder with restricted access. The anonymization table is built at this stage, where each contact is associated with an anonymous study I.D. number. A two-stage screening process will be used to select participants (timepoint T-1; Table 1). Initial contact will be made over the phone by a member of the research team. During this pre-screening call, only potential participants with no major physical or medical limitations to exercise and with access to the Internet and necessary technology will be selected. They will then receive the information and consent form by email, and the preliminary call will be scheduled with a member of the research team. During the preliminary call, the information and consent form will be presented to the potential participants, and they will be given the opportunity to provide oral consent. They will then be required to send written consent by email. If oral consent is obtained, the cognitive (MMSE) and physical (PARQ+) screenings will then be performed with a research assistant and will later be reviewed by a neuropsychologist and a kinesiologist, respectively. Once the research team receives the written consent by email and ensures eligibility, the participant will be considered enrolled. A technology tutorial will then be scheduled to ensure that Internet access and tools are ready and sufficiently mastered by participants. Collection of measurements and training data all along the study will be managed by assessors and trainers using online case report forms specifically dedicated to each testing session. Participants will receive automatic standardized communications by email to transmit study information like appointment schedules, links to self-reported questionnaires, and training guidelines. A non-overwriting process will ensure data integrity: all form submissions will be recorded in a journal fashion. Moreover, all data entries will be traceable and associated with a timestamp along with the identity of the research team member who completed the data entry. To ensure the blinding of the study, data collection will be divided into two sections on the online platform: training and evaluations. Research team members will receive different access based on their roles. The above-described procedure is summarized in Fig. 1.

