#### Planned data analysis

The variables in the study will be presented using descriptive statistics. The mean, standard deviation, median, minimum, Q1, Q3, and maximum will be presented for continuous variables. The number and percentage will be presented for nominal/ordinal variables. The statistical tests' assumptions will be examined, and data transformation or non-parametric analyses may be used as appropriate. SPSS and SAS version 9.4 or higher software will be used to conduct the analyses. Statistical tests will be two-tailed, and a *p* value of less than 0.05 will be considered as the indication of statistical significance.

Mean changes in cognitive performance from baseline will be analyzed using a repeated measures analysis of covariance (ANCOVA) model, adjusted for age, sex, education, and the dose of physical exercise, including the effects of the intervention (physical exercise alone or combined with cognitive training) and time (pre at baseline, mid at 3 months, post-intervention at 6 months). Observation of a statistically significant difference in the primary outcome between pre- and post-intervention timepoints will be considered as the evidence of the intervention's efficacy (i.e., primary hypothesis). The interaction between intervention arms (i.e., physical exercise alone or combined with cognitive training) and performance changes from pre to post-intervention will address the added value of the cognitive training compared to physical exercise alone (i.e., secondary hypothesis). Observation of a statistically significant *intervention × time* interaction in the primary outcome will be considered as the evidence that the differential effect operates by the exercises and combined interventions. Secondary and exploratory outcomes will be analyzed as the primary outcome.

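### One-leg stance, the only balance measure, stops at 60 s but is analysed as an ordinary mean change, so any balance effect is pulled toward zero to the extent that participants reach the limit

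*Protocol article*

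**What the plan says.** The abstract lists balance with a single instrument, "balance (one-leg stance test"), and places the Timed Up and Go and the 4-meter walk under gait and mobility. Secondary outcome—Physical functions sets the upper limit of that instrument: participants "stay on one leg as long as possible with a maximum duration of" 60 s.

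The population is described in the abstract as "One hundred twenty-two healthy older adults". The Participants section starts entry at age 50, excludes respiratory and cardiovascular disease, and requires "Absence of non-cardiopulmonary limitation to exercise (e.g., arthritis) or of a severe exercise intolerance". Recruitment is aimed at "active members of physical exercise centers" as well as at other community-dwelling adults (Remote setting and procedures, online data management).

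On analysis, mean changes from baseline in cognition "will be analyzed using a repeated measures analysis of covariance (ANCOVA) model", and then: "Secondary and exploratory outcomes will be analyzed as the primary outcome". The same section says that test assumptions will be examined and that transformation or non-parametric methods are available as an option. Dose-Response exploration applies a further repeated measures ANCOVA, by terciles of exercise dose, to primary and secondary outcomes. Ceiling effects are mentioned only for the computerised cognitive tasks.

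**The concern.** A stance time stopped at 60 s means at least 60 s. The stated model reads it as exactly 60 s. A participant at the limit at baseline can record only no change or a loss, whatever happens to underlying balance. Someone just below the limit can record only part of a gain.

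Three results are exposed: the pre-post change, which the plan uses as its evidence of efficacy; the arm-by-time interaction; and the dose-tercile contrast. The last has no protection from randomisation, because participants adjust their own dose. If fitter people exercise more, the high-dose tercile holds more participants at the limit. What is at stake is a null balance result that cannot be told apart from a ceiling effect.

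**Working it through.** **Inputs.** From the article: the 60 s limit, the mean-change model, and 49 analysed per arm (used here only as a group size; that calculation concerns cognition). The article gives no baseline distribution of stance time, no expected share at 60 s and no expected balance effect, so there is no balance figure to reproduce. Assumed: a normal latent balance score with baseline mean 0 and SD 1, a gain of 0.2 SD with exercise alone, a further arm difference of 0.3 SD, and a share *c* at the limit at baseline.

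**Formula.** The limit on the latent scale is k = Φ⁻¹(1 − c). If the latent mean moves from a to b with SD 1, the capped mean moves by the integral of Φ(k − m) over m from a to b. This does not depend on the pre-post correlation.

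**Worked case, c = 10%.** k = 1.282. For the arm difference, m runs from 0.2 to 0.5, so Φ(k − m) falls from 0.860 to 0.783. The integral is 0.247, and 0.247 / 0.3 = 82%.

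| Share at 60 s at baseline | Pre-post gain kept | Arm difference kept |
|---|---|---|
| 2% | 97% | 96% |
| 10% | 88% | 82% |
| 20% | 77% | 69% |
| 30% | 66% | 57% |
| 50% | 46% | 36% |

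A larger assumed arm difference of 0.483 SD gives similar values: 80%, 65%, 53% and 33% at 10%, 20%, 30% and 50%.

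**Dose terciles.** Simulated with test-retest correlation 0.7, a gain of 0.2 SD in the lowest tercile and a true high-minus-low difference of 0.30 SD. If dose is unrelated to balance, the observed difference is 0.25, 0.21, 0.15 and 0.11 at 10%, 20%, 35% and 50% at the limit. If dose correlates 0.5 with underlying balance, it is 0.17, 0.10, 0.03 and −0.02. That correlation is also an assumption.

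**Does the plan's fallback repair it?** No. Ranking or transforming leaves everyone at 60 s tied. In 600 simulated trials per setting (pre-post correlation 0.8, 49 per arm, latent difference 0.3 SD), a Mann-Whitney test on change rejected in 50%, 33% and 22% of runs at 10%, 30% and 50% at the limit; ANCOVA rejected in 61%, 49% and 37%. Part of that gap is the missing baseline adjustment, but the rank test clearly does not recover the loss.

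**Would a censored model help?** In the same runs, ANCOVA estimated 0.25, 0.17 and 0.11 of the latent 0.30. A Tobit model with baseline time and a baseline-at-limit indicator estimated 0.30, 0.29 and 0.29. Those data were generated from the Tobit model's own normal assumption. With a lognormal latent time, a Tobit on raw seconds kept 60%, 49%, 38% and 32% of the effect at 10%, 20%, 35% and 50%, against 49%, 32%, 19% and 11% for ANCOVA. A Tobit on log time kept about 94–103% of the log-scale effect.

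**False positives.** With no true arm difference, ANCOVA rejected in 4–6% of runs. The Tobit rejected in 6%, 5% and 9% at 10%, 30% and 50% at the limit.

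**The case against.** The strongest objection is that the share at 60 s is unknown. Eligibility and recruitment make a ceiling plausible, but there is no upper age limit and recruitment also reaches the wider community. A reader might infer that the balance effect will be understated as a matter of fact. The documents do not support that: at 2% the loss is small. This stands, and the point is therefore conditional.

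Second, mean stance time limited to 60 s is a legitimate quantity, and the loss exists only against an unlimited time that the protocol never names as its target. This also stands, and is why the planned ANCOVA can stay if it is described that way. It does not help a reader who takes a null result as no effect on balance.

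Third, a reader might infer that a censored model restores most of the lost power. Comparing an unadjusted change score with a baseline-adjusted Tobit would suggest so, but most of that gain is the adjustment. At 49 per arm, correlation 0.7 and a 0.483 SD difference, ordinary baseline-adjusted ANCOVA had power 90%, 86%, 79% and 56% at 10%, 20%, 35% and 50% at the limit; the Tobit had 92%, 86%, 82% and 72%. The case for the censored model rests on the estimate, not on power.

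Fourth, handling of capped values could sit in an analysis plan that is not shown, and the summary statistics already promised (Q3 and maximum) would reveal a large ceiling. That lowers the urgency. The article nevertheless does fix a default model that does not fit a limit it states itself.

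**Conclusion.** The point holds in conditional form. The article pairs a single balance test cut off at 60 s with a mean-change model that takes 60 s as the true time, and its optional fallback does not correct this. Under a normal latent score and the stated gains, the arm difference falls to roughly 80–35% of the latent one when 10–50% are at the limit at baseline, and hardly moves at 2%. The pre-post gain shrinks somewhat less. The dose contrast shrinks at least as much, and could vanish if dose tracks fitness.

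The cap dilutes the randomised comparison and does not produce false positives there. It would be wrong to read it as a threat to the primary conclusion, which concerns cognition: balance is one of several secondary physical measures. Nor do the documents support replacing the planned model outright, since the censored model brings its own assumption. This is a minor improvement to one secondary outcome.

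**What to change.** Keep the planned ANCOVA for one-leg stance and state that it estimates change in stance time limited to 60 s. Prespecify one supportive analysis for this outcome: a mixed Tobit-type model on log time, with baseline, 3-month and 6-month values all treated as right-censored at 60 s, and with time and arm-by-time terms so that both the pre-post gain and the arm difference are estimated. Add the corresponding dose-group terms for the dose-response analysis, and give a rule for zero times. A Tobit model of the 6-month value alone would not do: it drops the 3-month visit and does not estimate the pre-post gain. Report the number and percentage at 60 s by arm and visit.

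The cost is a few sentences of analysis text, with no new data and no change to the test. The downside is that the supportive result depends on the distribution assumed beyond 60 s. The simulations above used the single-visit version, so the mixed form should be checked for error rate before use, particularly if about half the sample is at the limit.

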#### Physical exercise

Participants will be encouraged to complete a home-based physical exercise using video capsules available via Facebook or Youtube, created by the Centre ÉPIC of the Montreal Heart Institute’s team of kinesiologists. The videos last approximately 15 min and include a 3- to 5-min warm-up, followed by a 10-min training, and finally by a 2-min cool-down period (https://tinyurl.com/epic-icm). The exercises do not require any equipment and comprise aerobic, muscular strengthening, flexibility, and/or balance exercises. For each exercise, several difficulty levels are described to allow participants to perform the exercise according to their physical capacities. Participants will be invited to perform exercise sessions at least 5 times per week and could be encouraged to do more during the weekly monitoring. This recommendation aims to provide a target for a minimal amount of physical exercise [30] that all participants can introduce and autonomously maintain in their routine regardless of the sanitary context, their initial physical condition, or prior exercise routine. The exercise sessions can be performed at home using the video capsules, as well as other video or web-based training programs. As sanitary measures and confinement regulations could change during the course of the study, participants could also engage in outdoor activities (e.g., walking or cycling). For each exercise session, participants have to report its duration, intensity, and the nature of the activity via a follow-up agenda that will be provided by their training coach. Participants will assess the intensity of their exercise using the modified Borg Rating of Perceived Exertion (RPE) graduated from 0 to 10, where 0 indicates low and 10 high intensity.

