##### Dose-Response exploration

The type of activity, its frequency, duration, and intensity (i.e., according to the Borg scale) will be considered to compute the dose of physical exercise. The weekly dose of physical exercise will be converted in kcal and in METs using the Compendium of Physical Activities (i.e., coding scheme classifying specific physical activities by their rate of energy expenditure) [68, 69]. The effect of physical exercise dose on cognitive and physical functions will be evaluated according to participants’ mean weekly dose during the 6 months of intervention. Based on the overall study sample distribution, participants will be classified into three groups: higher, medium, and lower doses of physical exercise (i.e., tercile split). How the dose of physical exercise affects the primary and the secondary outcomes will be addressed by a repeated measures ANCOVA model, adjusted for age, sex, and education, including the effects of the intervention (physical exercise alone or combined with cognitive training), time (pre at baseline, mid at 3 months, post-intervention at 6 months) and dose groups (lower, medium or higher doses). An exploration of the dose-response effect for cognitive training will also be performed within the combined physical exercise and cognitive training intervention group. The dose of cognitive training will be considered according to its mean weekly duration. How the dose of cognitive training affects the primary and the secondary outcomes will be addressed by a repeated measures ANCOVA model, adjusted for age, sex, education, and the dose of physical exercise, including the effects of time (pre at baseline, mid at 3 months, post-intervention at 6 months) and dose groups (lower or higher doses of cognitive training; median split).

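### The Matthews fitness estimate and the exercise dose both contain self-reported activity, so the dose-response test and the pre-post change in this one secondary outcome can be partly formula-driven

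*Protocol article*

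**What the plan says.** **Outcome.** Under Secondary outcome—Physical functions, cardiorespiratory fitness is not measured. It is predicted by the Matthews questionnaire, "based on sex, age, anthropometric data, and self-reported physical activity level". Table 1 places the questionnaire among the online self-reported forms, at baseline, 3, 6 and 12 months.

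**Dose.** Under Physical exercise, for each session "participants have to report its duration, intensity, and the nature of the activity via a follow-up agenda". The Dose-Response exploration builds the exposure from these reports: "The type of activity, its frequency, duration, and intensity (i.e., according to the Borg scale) will be considered to compute the dose of physical exercise". It is then converted to kcal and METs week by week, averaged over the six months and split into terciles.

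**Models.** The Dose-Response exploration states: "How the dose of physical exercise affects the primary and the secondary outcomes will be addressed by a repeated measures ANCOVA model". Under Planned data analysis the main model is "adjusted for age, sex, education, and the dose of physical exercise, including the effects of the intervention" and time, and "Secondary and exploratory outcomes will be analyzed as the primary outcome". Neither section exempts the Matthews estimate.

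**Limitation.** The study limitation section concedes that equations of this type can misjudge change in fitness. It does not mention that the outcome and the dose share content.

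**The concern.** In the dose-response analysis, one ingredient of the outcome is the same kind of information as the exposure: what participants say about their own activity. Someone who reports more exercise is likely to fall in a higher dose tercile and, if the questionnaire answers move the same way, also gains predicted VO2max through the equation. That gain appears whether or not fitness has changed.

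The pre-post comparison has a related weakness. Participants know which training they receive, coaches call every week to encourage exercise, and there is no untreated control group. A rise in reported activity raises the estimate, and nothing in the design separates that from a fitness gain.

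At stake is a published statement that more home exercise, or the programme itself, improved fitness, when the result may partly restate what participants reported. The limitation section also offers the dose-response analysis as partial compensation for having no control group, so a built-in dose effect weakens that argument for this outcome.

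**Working it through.** The article gives no figure for this outcome, so there is none to reproduce. Its sample size calculation concerns cognition and supplies only the number of completers: 2 × 49 = 98.

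**Step 1: what can move the estimate.** For illustration, write the prediction as a weighted sum of sex, age, anthropometrics (B) and reported activity (A). The form and weights of the equation are not in the article. From baseline to 6 months:

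predicted change = (age weight × 0.5 year) + (activity weight × change in A) + (anthropometric weight × change in B)

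Sex cancels, and the age term is the same for everyone. Differences between participants in predicted change therefore come only from reported activity and anthropometrics.

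**Step 2: whether age and sex adjustment matters.** In a simulation with age and sex in the equation, the slope of predicted change on dose was 0.402 without and 0.402 with adjustment for them. That adjustment is not part of the problem.

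**Step 3: correlation produced by reporting.** Let ρ be the correlation of logged dose with change in reported activity, and k the correlation of that change with predicted change. If dose has no effect on true fitness and the link runs only through reporting, dose and predicted change correlate at r = ρ × k. For example, ρ = 0.2 and k = 0.5 give r = 0.1. Neither ρ nor k is in the article, so r is an assumption shown over a range.

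**Step 4: consequence for the planned tercile split.** The simulation uses 98 completers, normal variables, three dose groups and a one-way F test on the 6-month change at 0.05. As a check, the mean of a standard normal in its outer terciles is ±1.091, which gives

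λ = (98/3) × 2 × (1.091 r)² / (1 − 0.793 r²), where 0.793 = (2/3) × 1.091²,

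referred to a noncentral F with 2 and 95 degrees of freedom.

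| Assumed r | λ | Rejection, noncentral F | Rejection, simulated |
|---|---|---|---|
| 0 | 0 | 5% | 5% |
| 0.1 | 0.78 | 11% | 11% |
| 0.2 | 3.21 | 33% | 33% |
| 0.3 | 7.53 | 68% | 66% |
| 0.5 | 24.2 | 99% | 99% |

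A fitness change measured independently of reported activity was rejected in 4% to 6% of simulated trials. The F test on change simplifies the planned three-timepoint model, so the figures are illustrative.

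**Step 5: the main model.** There, dose is a covariate, not the tested factor. It still shares content with this outcome, so it can absorb part of a difference in estimated fitness between arms.

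**The case against.** **The size of r is unknown and may be small.** Dose is an average level over six months taken from agendas, whereas the Matthews form is a separate questionnaire and the test concerns change. Recruitment reaches active members of exercise centres. Such a person can log a high dose while reporting the same activity as at baseline, and the estimate then does not rise. This stands, and it is why the range includes 0 and 0.1.

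**The weakness is partly disclosed.** The measure is labelled as estimated throughout, and the limitation section warns of error in estimated change. That also stands, but general prediction error and shared content act differently. Random error would tend to weaken a dose effect, whereas shared content can create one.

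**The scope is narrow.** The dose-response analysis is exploratory, and the efficacy rule under Planned data analysis is worded for the primary outcome, cognition. This is correct and limits the weight of the point.

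A reader might infer four stronger things that the article does not support:

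- *The estimate says nothing about fitness.* The limitation section cites evidence that changes in such equations were associated with measured change, although with significant errors.
- *Adjusting for age and sex adds to the circularity.* Step 2 shows that it does not.
- *The arm comparison is spoiled too.* The exercise component is the same in both arms, so reporting inflation from it is expected in both, and no mechanism for a false arm-by-time effect has been shown.
- *The false-positive rates are higher still.* A Fisher-z calculation for a continuous dose gives 51% and 85% at r = 0.2 and 0.3, but the plan uses terciles.

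**Conclusion.** The point holds for two uses of one secondary outcome. The dose-group test on Matthews-predicted VO2max has self-reported activity on both sides, and its pre-post change can rise through reporting alone. A significant result in either could not separate a fitness gain from a change in reported activity, and the stated limitation does not cover this.

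The excess of false positives cannot be computed from the article. Under assumed reporting-only correlations of 0.1 to 0.5, with 98 completers, no true dose effect on fitness and a simplified tercile test, rejection runs from about 11% to 99% against a nominal 5%. With no such correlation it stays at 5%.

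Cognition and the four performance tests are unaffected, and the randomised between-arm comparison of estimated fitness is not shown to be biased. The point deserves correction but does not threaten the trial's main conclusions.

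**What to change.** 1. In the Dose-Response exploration, exclude the Matthews estimate from the secondary outcomes tested against exercise dose.
2. Under Planned data analysis, fit the model for this outcome without the dose covariate.
3. Keep its between-arm comparison as a secondary result, labelled as activity-based estimated fitness.
4. State that its pre-post change will not be interpreted as a measured fitness gain.
5. Base dose-response and pre-post conclusions on physical function on the Timed Up and Go, 4-meter walk, five-time sit-to-stand and one-leg balance tests, all already collected.
6. Add the overlap between dose and predicted fitness to the limitation section.

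No new data are needed. The cost is that one secondary outcome drops out of an exploratory analysis. Because the Ethical considerations section requires ethics board approval even for minor changes, an amendment may be needed. Removing the estimate from all inference would go further than the problem warrants, since it would also discard the between-arm comparison.
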